# ABSTRACT

The Xpert™ MTB assay is a rapid automated test (under 2 hours) for the detection of M. tuberculosis (MTB) and rifampicin resistance. The assay has undergone clinical validation in reference settings in South Africa, India, Peru, Germany and Azerbaijan. The assay was found to be highly sensitive and specific, detecting M. tuberculosis DNA in almost all smear-positive sputum specimens and 90% of smear-negative, culture-positive specimens. Thus the Xpert™ MTB appears to be suited for both rapid MDR screening as well as early case detection in smear negative TB patients. It is anticipated that the system will allow for on-the-spot diagnosis and TB treatment initiation based on one Xpert result. These findings need now to be confirmed in the intended setting of use.

STUDY DESIGN (3 phases)

1. Validation Phase (3 months enrolment): This validation phase aims to collect baseline data for the validation of Xpert™ MTB performance in this new environment. Test results not used for patient treatment.

2. Implementation Phase (3 months enrolment): Smear microscopy and Xpert™ MTB/Rif are used for TB treatment decisions. Culture will be performed by the reference laboratory for all cases.

3. Continuation Phase (6 months enrolment): Smear microscopy and Xpert™ MTB/Rif are used for TB treatment decisions. Selected conventional DST is done only for Xpert™ Rif resistant cases.

Patients included will be those with a clinical suspicion of pulmonary TB as well as those at risk of MDR-TB. Children <18 yrs and patients already on TB therapy will be excluded.

Sample collection and analysis

Sputum samples for investigation will be collected following standard practice at the clinic. Xpert™ MTB will be done on site (Khayelitsha) or at the local NHLS laboratory (Paarl). Samples from at least 150 patients will be evaluated per month, giving a total of at least 1800 patient samples. Patients will follow the normal flow within the clinic. Testing will be integrated into the routine activities of the clinic.

INTRODUCTION

Despite the enormous global burden of TB, approaches to TB diagnosis still rely on traditional methods that have major limitations. The disproportionate amount of smear-negative disease in sub-Saharan Africa, which shoulders two-thirds of the global burden of HIV/AIDS, has greatly complicated TB case detection and disease control. Multidrug-resistant (MDR) TB, defined as resistance to both isoniazid and rifampin, two of the most important “first-line” anti-TB drugs, is a rapidly growing problem, both in Eastern Europe and countries with high HIV prevalence. Even more alarming is the recently documented phenomenon of XDR (or extensively drug-resistant) TB, defined not only as resistance to isoniazid and rifampin but also to one second line injectable agent and a fluoroquinolone antibiotic. XDR TB is associated with significantly poorer treatment outcomes than MDR TB.

The low sensitivity of smear microscopy limits its impact on TB control. Culture methods are complex, slow and still only scarcely available in high endemic-countries. Drug susceptibility testing is even slower and more technically complex. While patients await diagnosis, their disease progresses with an increased chance of dying from tuberculosis and they continue to transmit drug-resistant TB to others, especially family members.

Early case detection is essential to interrupt transmission and to prevent the further spread of tuberculosis and multidrug-resistant tuberculosis. A new diagnostic approach is therefore urgently needed.

Only a small fraction of the estimated 489,000 MDR TB cases occurring each year have access to drug susceptibility testing DST. Key obstacles to DST expansion over the past years were 1) the complexity of available tools and the laboratory infrastructure required for their implementation; 2) the unaffordable price of better (but equally complex) technologies; and 3) the unavailability of rapid and simple tools for identification of resistance.

Although nucleic acid amplification tests (NAAT) for the rapid detection of TB and rifampicin resistance exist, their complexity, along with the labor demands, including the need for a high degree of technical support and well-trained staff, make them suitable for central reference laboratories only.

**DESCRIPTION OF Xpert™ MTB/Rif TEST**

The Xpert™ MTB/Rif assay performed on the GeneXpert™ MTB/Rif system is a rapid test for the detection of *M. tuberculosis* (MTB) and rifampicin resistance. The GeneXpert™ system consists of a GeneXpert instrument, personal computer and disposable fluidic cartridges. The system combines cartridge-based sample preparation with amplification and detection in a fully integrated and automated nucleic acid analysis instrument.

**CLINICAL PERFORMANCE OF Xpert™ MTB/Rif TEST**

After completion of development, the assay has undergone clinical evaluation in a statistically powered number of patients in reference settings in South Africa, India, Peru, Germany and Azerbaijan. As summarized in the table below, the Xpert™ MTB/Rif assay was found to be highly sensitive and specific, detecting *M. tuberculosis* DNA in almost all smear-positive sputum specimens and a very high percentage of smear-negative, culture-positive specimens. Rifampicin resistance and MDR was detected with high accuracy. Assay performance even remained good when analyzing a single Xpert™ MTB/Rif result in comparison to 4 culture results per patient. The performance was very homogenous across countries.

|  | Sensitivity  in S+C+ | Sensitivity  in S-C+ | Specificity  in Non-TB |
| --- | --- | --- | --- |
| Total | 99.5%  [98.4% - 99.8%] | 90.0%  [84.6% - 93.7%] | 97.9%  [96.4% - 98.8%] |

**Table: Per patient analysis, Xpert™ MTB/Rif sensitivity and specificity (3 Xpert, 3 smears, 4 cultures), preliminary study results.**

|  | Sensitivity in Rif resistant cases | Sensitivity in MDR cases | Specificity in Rif sensitive cases |
| --- | --- | --- | --- |
| Total | 96.1%  [92.4% - 98.0%] | 96.5%  [93.0% - 98.3%] | 98.6%  [97.2% - 99.3%] |

**Table: Per patient analysis, Xpert™ MTB/Rif sensitivity and specificity for Rif and MDR detection (3 Xpert, 3 smears, 4 cultures), sequencing data not taken into consideration; preliminary study results.**

In conclusion, Xpert™ MTB/Rif was not only suited for rapid MDR screening, but also seemed very useful for early case detection in smear negative TB patients. The high accuracy of a single Xpert™ MTB/Rif result per patient and the time to diagnosis of below 2 hours should allow for on-the-spot diagnosis and TB treatment initiation based on one Xpert™ MTB/Rif result only. These findings need now to be confirmed in the intended setting of use.

We will inform you as soon as the submitted manuscript with evaluation study results has been accepted for publication.

## MOTIVATION

In response to the growing problems of MDR and XDR TB, as well as the continuing epidemic of HIV-associated TB, WHO and its partners have called for greatly enhanced global capacity for mycobacterial culture and DST as well as for implementation of rapid methods for screening for MDR TB. This massive scale-up is thought to require that up to 2000 new culture-capable TB laboratories be established and 10,000 new laboratory workers be trained by 2015.

It is possible that much of this needed capacity could be addressed by molecular tests for case finding and MDR TB detection. With the WHO endorsement in 2008 of line probe assays (LPAs) for MDR TB screening, many countries are implementing this system. However, as noted above, the test is sufficiently complex that decentralized testing is not feasible. Therefore, the Xpert™ MTB/Rif assay is of great interest as it provides for highly accurate and simplified testing at a much lower level of the health system. Although it provides information only on rifampin resistance (in addition to detection of *M. tuberculosis* complex), in nearly all settings rifampin resistance is an accurate surrogate for MDR TB.

Although good performance of the Xpert™ MTB/Rif assay has been demonstrated in carefully controlled laboratory settings, data on testing in program conditions, as well as information about cost and patient/public health impact, are needed to inform public policy on the use of the system. These demonstration projects are intended to provide this information.

It is proposed that the Western Cape will be one of the demonstration sites for this multi-centre study. The partners will be the National Department of Health, the University of Cape Town, Médecins Sans Frontières, the National Health Laboratory Service (NHLS) and the Foundation for Innovative New Diagnostics (FIND).

## AIMS

The purpose of this demonstration project is to assess the implementation of Xpert™ MTB/Rif in decentralized laboratories in low- and moderate-income settings. The project aims at a) confirming the Xpert™ MTB/Rif performance in decentralized laboratories and b) demonstrating the feasibility, impact and cost-efficiency of using Xpert™ MTB/Rif at lower levels of the health system for enhanced detection of smear-negative TB and MDR TB. The data will be reported to national public health authorities and WHO in order to inform policy decision.

**Study hypothesis**

Fully automated molecular testing with integrated specimen processing by Xpert™ MTB/Rif is easy and robust enough to be decentralized and allows to significantly increase case detection rates for TB and MDR TB, as well as to shorten time to treatment initiation in comparison with the conventional diagnostic algorithm. Patient management based on a single Xpert™ MTB/Rif test, carried out while the patient is waiting for his/her result, decreases the drop out rate prior to diagnosis and the costs and barriers for the patient. The introduction of such testing may therefore be cost-effective for the health system when compared to conventional culture and DST costs.

**SPECIFIC OBJECTIVES**

1. **Clinical performance**
   - Measure increased yield in TB and MDR TB case detection rates compared to local routine diagnostic algorithm
   - Determine sensitivity and specificity compared to central culture and DST (preferable on liquid media).
2. **Operational performance**

- Assess robustness of Xpert™ reagents and equipment, maintenance and customer support needs, as well as minimal training needs
- Develop recommendations on how to integrate automated molecular testing in resource – poor countries using existing diagnostic algorithms for case detection and MDR TB screening.

1. **Cost-efficiency**

- Quantify “per test” and “per patient” costs for the health system compared to routine culture and DST

## METHODS

## Study design

The demonstration project will primarily assess the feasibility of using Xpert™ MTB/Rif in district laboratories.

## Study design

The demonstration project will primarily assess the feasibility of using Xpert™ MTB/Rif in district laboratories.

**Training & proficiency testing** (3-5 days):

During the on-site training phase, lab technicians from the district laboratory and the supervisor from the reference laboratory will receive training on the Xpert™ MTB/Rif assay from the FIND study coordinator. The competency if the staff to perform the assay will be assessed using stored, previously cultured samples from the evaluation study.

**Evaluation study (52 weeks)**

The study has been designed in a cluster randomized fashion, with each week considered as a separate cluster. Eligible TB suspects will be treated either on the basis of standard microscopy +/- culture and susceptibility testing (**Routine Arm**), or will be treated on the basis of the Xpert assay (**Xpert Arm**, with Xpert at times performed in conjunction with microscopy and culture as detailed below). The laboratory testing algorithm will alternate between Xpert and standard of care on a weekly basis, and the results sent back to the clinic will be acted upon irrespective of the test method. There are different phases to the study, as outlined in the table below.

**Phase 1:** 16 weeks

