**Xpert Arm (plus culture):**

2 sputum samples per patient

- 1 sputum for Xpert at routine laboratory
- 1 sputum for smear and culture at reference laboratory (DST performed if clinical suspicion of MDR-TB, or if Xpert test shows rifampicin resistance)

Treatment based on Xpert result, or culture result (in cases of Xpert negative, culture positive). Xpert or culture positive patients followed up at 2 and 6 months. Smear negative and Xpert negative patients asked to return if symptoms persist.

Phase 1 will allow us to evaluate the performance of the Xpert system in a clinic setting. The additional cultures performed will allow us to determine whether the performance of the assay in a routine setting is comparable to the performance described in a research setting. These are as described in Objectives 1b and 2a.

**Phase 2:** 16 weeks

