**Routine Arm:**

2 sputum samples per patient

- 1 sputum for microscopy at routine laboratory
- 1 sputum for microscopy (routine laboratory), or microscopy plus culture +/- susceptibility testing (reference laboratory) at the clinic discretion (i.e., following standard practice)

Treatment based on microscopy and/or culture results, as per routine practice. Patients followed up at 2 and 6 months if they are smear or culture positive. Smear negative patients asked to return if symptoms persist. Smear negative, culture positive patients will be traced if possible.

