**Xpert Arm:**

- 1 sputum for Xpert at routine laboratory
- 1 sputum for microscopy if Xpert positive, and for microscopy plus culture and DST if Xpert shows rifampicin resistance. The purpose of microscopy for the Xpert positive sputa is to provide a baseline microscopy result for follow-up purposes, as the national TB programme performs smear microscopy at follow up on smear positive cases. Xpert negative cases will have no culture performed.

Treatment based on Xpert results, Patients followed up at 2 and 6 months if they are Xpert positive. Xpert negative patients asked to return if symptoms persist.

Phase 2 is designed to assess the impact that introduction of the Xpert test will have on diagnosis and management of TB, as outlined in Objective 1a. Information from both this phase and phase 1 will be used to quantify the cost-effectiveness of the assay (Objective 3)

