**Data collection**:

During phases 1 and 2, data will be collected at first presentation for all TB suspects, and data will be collected at the 2 and 6 month follow up visits for Xpert and/or smear and/or culture positive patients. The data in the CRF will be data that is normally collected as part of routine clinical practice. The purpose of the CRF is to allow us to record in a central database information that will allow us to assess the impact of the study in particular. This information thus includes how the diagnosis of TB was made, when TB was diagnosed, when a diagnosis of drug resistant TB was made, what additional investigations were performed, clinical response to therapy, HIV status when known.

**Phase 3:** 20 weeks

**No randomization**.

2 sputa per patient

- 1 sputum for Xpert at routine laboratory
- 1 sputum for microscopy if Xpert positive, and for microscopy plus culture and DST if Xpert shows rifampicin resistance. The purpose of microscopy for the Xpert positive sputa is to provide a baseline microscopy result for follow-up purposes, as the national TB programme performs smear microscopy at follow up on smear positive cases. Xpert negative cases will have no culture performed.

Treatment based on Xpert results, Patients followed up as per routine clinic practice (which may mirror the 2 and 6 month follow up described above, but case report forms will not be completed at these follow up visits)

Phase 3 will (in conjunction with phases 1 and 2) provide the best opportunity to develop recommendations on the integration of the Xpert assay into the routine diagnostic algorithm and will allow assessment of introduction of Xpert on clinic and laboratory workload.

Inclusion criteria

- Clinical suspicion of pulmonary TB (not on TB treatment)
- Re-treatment cases
- Relapses
- Non-converting PTB cases > 2-3 months
- Symptomatic contacts of known MDR cases

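### The comparison is labelled cluster randomised, but allocation is weekly alternation: later weeks are predictable, and no rule says which arm a returning patient counts in.

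*Protocol*

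**What the plan says.** Protocol, Evaluation study (52 weeks), states: "The study has been designed in a cluster randomized fashion, with each week considered as a separate cluster". Two sentences later it gives the rule: "The laboratory testing algorithm will alternate between Xpert and standard of care on a weekly basis". It adds that "the results sent back to the clinic will be acted upon irrespective of the test method". No random sequence, random starting arm, list holder or concealment is described anywhere.

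The two-arm comparison covers "Phase 1: 16 weeks" and "Phase 2: 16 weeks". "Phase 3: 20 weeks" is a single-arm Xpert period marked as not randomised, which implies that the two earlier phases are. Ethical Considerations also relies on randomisation to justify the control arm.

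On returning patients, the Phase 2 Routine Arm says "Smear negative patients asked to return if symptoms persist" and the Phase 2 Xpert Arm says "Xpert negative patients asked to return if symptoms persist". Phase 1 has similar instructions. No return interval is given, and nothing says which arm a returner belongs to.

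**The concern.** Randomising weeks would justify treating Xpert weeks and routine weeks as comparable apart from chance. Alternation does not provide that. Someone who knows this week's arm also knows next week's, and an Xpert week is never more than one week away. Whether a patient is a TB suspect, and on which day sputum is sent, depends partly on staff judgement. The protocol itself describes Xpert as probably the better test (Ethical Considerations). Foreknowledge, discretion and a preference could therefore shift likelier cases into Xpert weeks.

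At stake are Objective 1a (increased yield over the routine algorithm), which Phase 2 is designed to address, and the claim in the Study hypothesis of shorter time to treatment. The Phase 1 between-arm comparison has the same weakness. The results are intended to inform WHO and national policy, where the word randomised will carry weight.

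A second route to error is the returning patient. Without a counting rule, one person can appear in both arms, and a case missed in one arm can be credited to the other.

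**Working it through.** **1. Does the protocol's own figure fit exact alternation?** Under Sample size it expects 1600-1800 Xpert tests from 32 Xpert weeks at 45-50 suspects per site per week.
- As written: 32 × 45 = 1440 and 32 × 50 = 1600. This does not reproduce 1600-1800.
- With 1:1 alternation in the two 16-week phases plus Phase 3: 8 + 8 + 20 = 36 Xpert weeks; 36 × 45 = 1620 and 36 × 50 = 1800. This reproduces the range, for one site.

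So the test count agrees with eight weeks per arm per phase. The mismatch between 32 and 36 weeks is a separate matter, and nothing below depends on it.

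**2. Predictability over a 16-week phase.**
- Alternation: 2 possible sequences. If only the first week must be guessed, the share of weeks known in advance is (0.5 + 15)/16 = 96.9%. It is 100% once any week is known. A random start would not change this after week 1.
- Permuted blocks of 4: C(4,2)^4 = 6^4 = 1,296 sequences. Expected correct guesses per block are 1/2 + 2/3 + 2/3 + 1 = 2.83 of 4, about 71%.
- Unrestricted order of eight and eight weeks: C(16,8) = 12,870 sequences; about 63% guessed correctly by simulation.

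**3. Returning patients.** Chance that the return visit falls in an opposite-arm week:

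| Allocation | 1 week later | 2 weeks | 3 weeks | 4 weeks |
| --- | --- | --- | --- | --- |
| Alternation | 100% | 0% | 100% | 0% |

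For a return one week later, blocks of 4 give (12 × 2/3 + 3 × 1/2)/15 = 63%, and unrestricted order gives 8/15 = 53%. Randomising weeks lowers this crossover but does not remove it.

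**4. Size of a possible selection effect (illustration).** Let N be suspects per site-week, p the TB prevalence, m the patients moved from each routine week to the next Xpert week, and q their probability of TB. With no test effect at all:

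false difference = (pN + mq)/(N + m) − (pN − mq)/(N − m)

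N = 47.5 is the midpoint of the protocol's 45-50. The values of p, q and m are assumptions; the protocol gives none of them.

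| p | q | m | Xpert weeks | Routine weeks | Difference |
| --- | --- | --- | --- | --- | --- |
| 20% | 50% | 1 | 10.0/48.5 = 20.6% | 9.0/46.5 = 19.4% | +1.3 points |
| 20% | 50% | 2 | 10.5/49.5 = 21.2% | 8.5/45.5 = 18.7% | +2.5 points |
| 20% | 50% | 3 | 11.0/50.5 = 21.8% | 8.0/44.5 = 18.0% | +3.8 points |
| 10% | 70% | 2 | 6.15/49.5 = 12.4% | 3.35/45.5 = 7.4% | +5.1 points |
| 40% | 30% | 2 | 19.6/49.5 = 39.6% | 18.4/45.5 = 40.4% | −0.8 points |

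The last two rows are the extremes for m = 2 over p of 10-40% and q of 30-70%. The sign turns negative when those moved are less likely to have TB than the average suspect.

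**The case against.** The case for leaving the design alone has real content.

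- **Much of the study is untouched.** In Phase 1 every Xpert-arm patient also has smear and culture, so accuracy, and Xpert against smear within the same patient, do not depend on allocation. Operational objectives and Phase 3 are also outside the problem. This stands. Phase 1 also has culture in both arms, so culture positivity by arm can check case mix there. Phase 2 has no such check: Xpert-negative patients are not cultured, and routine culture is at the clinic's discretion.
- **Foreknowledge and deferral are inferred.** The rule is a laboratory switch, and the protocol does not say that clinics receive the schedule. Patients follow normal clinic flow, consent is waived, and routine-arm patients suspected of MDR-TB can already get culture and susceptibility testing. A reader might infer that staff will know the arms and will hold cases back. The documents do not show that; they show only that nothing prevents it.
- **Crossover cuts both ways.** A reader might infer that returning patients systematically favour Xpert. The text does not support that: even-week returns stay in the same arm, and an Xpert miss can equally be credited to routine. Data collection at first presentation hints at indexing there but states no rule. How returners are analysed may be settled in a SAP that is not shown, so this part is secondary to the allocation rule, which the protocol itself fixes.
- **Calendar effects.** It is tempting to say that month-end effects attach to one arm. A month is about 4.35 weeks, so month-ends do not stay on odd or even weeks, and alternation balances slow trends well. That argument fails.
- **Phase 2 as the only controlled evidence.** This is also too strong, because Phase 1 has two alternating arms as well.

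**Conclusion.** The point holds in limited form. The label and the allocation rule contradict each other within one paragraph, and other sections lean on the label. Between-arm comparisons of yield and time to treatment in Phases 1 and 2 are open to selection bias through predictable allocation, and it is undefined which arm a returning patient counts in. Phase 2 is the more exposed because it lacks universal culture.

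The size is not known. The 2.5-point figure is correct arithmetic on assumed inputs (20% prevalence, 50% probability of TB in those moved, two moved per routine week). It shows that a few deferred patients per week could matter; it does not estimate what will happen. Over the assumed ranges it runs from about −0.8 to +5.1 points.

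**What to change.** - **Allocation.** Keep the week as cluster, but randomise the order of weeks in permuted blocks (for example, of 4), separately for Khayelitsha and Paarl and within Phases 1 and 2. Someone outside the clinics holds the list and releases each arm only at the start of its week.
- **Counting.** State that each patient is counted and analysed once, in the arm of the week of first presentation, whatever test is used at a later visit, and that crossovers are recorded. This is needed alongside the random list, because blocks of 4 still leave a 63% chance that the next week is the opposite arm.
- **If alternation is kept.** Replace the term cluster randomized with *alternating-week (quasi-randomised) allocation* wherever the design is described, bring the references to randomisation under Phase 3 and in Ethical Considerations into line, and limit the conclusions on yield and time to treatment accordingly.

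The cost is a computer-generated list and a protocol paragraph. The laboratory must follow a list and may run the same algorithm in consecutive weeks. Blocks reduce predictability (about 71% of weeks guessable against about 97%) but do not remove it, which is why release at the start of each week matters.
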